#### Exclusion Criteria

The exclusion criteria are as follows: (1) Age less than 18 years; (2) Diagnosis (current unless otherwise stated) of a neurological disorder (including a history of seizures), a primary or secondary tumor in the central nervous system, cerebrovascular disease, stroke, cerebral aneurysm, or movement disorder; (3) Diagnosis of a current psychotic disorder, such as substance-induced psychosis, psychotic disorder due to a medical condition, or MDD with psychotic features at the time of screening; (4) Diagnosis of a current personality disorder that may hinder participation in this research or may have the potential of affecting cognition and the ability to fully participate in the study; (5) Presence of a learning disability as identified through medical history or by the investigator during the assessment process; (6) Involvement in any drug or device clinical trial within the last 6 weeks before the screening visit or involvement in another clinical trial for the duration of this study; and (7) Identification of or the sudden appearance of any condition identified by the investigators to have the potential to hinder the progress and completion of the trial, or be a confounding factor for the outcome assessment.

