### Recruitment Process

Participant eligibility will be determined by the rTMS specialist team within the various centers. If found eligible for inclusion in the rTMS program, the patient will be approached by a member of the study team to introduce the study. A copy of the information leaflet will be provided to patients to have a detailed insight into the study processes. Once the patients agree to take part in the study, they will be asked to sign a consent form. The signing of the consent form and recruitment process will be conducted face-to-face at the various study sites during the week of the rTMS eligibility assessment of the participants, which usually occurs 1 week before the rTMS sessions begin. Participation in the study is by choice, and a participant can decide to withdraw at any time without providing a reason. To withdraw from the study, participants can contact the research coordinator to communicate their decision to discontinue their participation in the study. Once withdrawn, the study will not collect any new information about them, and if deemed fit, the said participants may approach the research team to withdraw all data collected on them before the study data are analyzed or disseminated.

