### Randomization and Blinding

A simple randomization technique will be employed using a single sequence of random assignments. The simple randomization will be performed using a computer-generated Excel sheet (Microsoft Corp). To ensure balance (1:1), the randomization will be stratified by using permuted blocks. The codes generated will then be transmitted via text message by an independent statistician directly to a blinded researcher’s password-protected phone line with a secure online backup. This process will occur for enrollment as each participant signs the consent form.

Since blinding of participants in this study is impossible, their treatment allocation will be made known to them right after the randomization process. Primary outcome assessors will not be granted access to the database that contains the randomization codes, and they will not be involved with all discussions concerning the study participants and may be blinded to the treatment arm allocations. The data that would be generated from the study will undergo a blind review for the reason of finishing the planned analysis.

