### Interventions

Study participants will be randomized to 1 of 2 treatment interventions (rTMS alone or rTMS plus Text4Support). During the introductory visit to the study sites, participants in both arms of the study will be given a detailed orientation about the rTMS application, and all procedures and activities within each visit will be explained to them. As part of their participation in the rTMS program, all patients will be made to complete some standard measures. Participants will be invited to the various rTMS clinics a week before the commencement of the rTMS sessions to enable them to undergo motor threshold (MT) assessment. MT assessment is essential in that it aids in the selection of the required stimulation intensity for each patient for inclusion in the treatment. It is a measure of the minimum intensity of TMS output needed to elicit a motor response in the participating TRD patients in at least 50% of all attempts.

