Additionally, participants in the rTMS plus Text4Support group of the study will be assisted by a study team member to register into the Text4Support program. The process will require all participants in this arm of the study to input their phone numbers into the Text4Support platform, which will be used to deliver daily messages. Starting a day after enrollment, participants will receive daily supportive text messages designed by mental health therapists, clinical psychologists, psychiatrists, and mental health service users. These messages will be based on cognitive behavior therapy principles crafted to positively enhance the mood of users with depressive symptoms and other related mental health problems of concern. The messages will be preprogrammed into a software program that will deliver the messages automatically to the participants’ mobile phones at 10 AM (Mountain Time) and 12 PM (Atlantic Time), and each participant will receive these messages continuously for 6 weeks.

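### The arm is assigned and disclosed at consent, usually about a week before rTMS begins, so patients lost in that open-label week are already randomised and know their arm

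*Protocol article*

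**What the plan says.** The sequence has to be put together from four sections of the protocol article.

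- **Recruitment Process.** The rTMS team settles eligibility, and only then is the patient approached: "If found eligible for inclusion in the rTMS program, the patient will be approached by a member of the study team to introduce the study". Consent is signed "during the week of the rTMS eligibility assessment of the participants, which usually occurs 1 week before the rTMS sessions begin". A participant may withdraw at any time. No new information is then collected, and the participant may also ask to have data already collected withdrawn, up to the point of analysis or dissemination.
- **Randomization and Blinding.** On release of the code: "This process will occur for enrollment as each participant signs the consent form". Because participants cannot be blinded, "their treatment allocation will be made known to them right after the randomization process".
- **Interventions.** In the Text4Support arm: "Starting a day after enrollment, participants will receive daily supportive text messages". Participants attend the clinic "a week before the commencement of the rTMS sessions to enable them to undergo motor threshold (MT) assessment". All are scheduled for 30 rTMS sessions over 6 weeks.
- **Data Analysis.** The analysis follows intention to treat. Sensitivity analyses of covariance carry the last observation forward for missing data.

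**The concern.** The trial asks whether Text4Support improves the response to rTMS. Both arms are meant to receive rTMS, and only the texts differ. With allocation at the signature there is usually about a week in which a participant knows the arm but has not had the treatment that the texts are meant to augment. Two kinds of patient can arise in that week.

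- **Those who withdraw.** They are randomised but contribute no later outcome, and perhaps no data at all. A patient told that they are in the rTMS-alone arm may be more or less likely to leave than one already receiving texts. If so, the loss differs by arm, and it follows from knowledge of the allocation.
- **Those who never start rTMS but stay in follow-up.** Intention to treat rightly keeps them, but they compare texts with no texts in the absence of rTMS, which is not the stated question.

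The article also intends the results to supply effect-size data for a full-scale trial (end of the Introduction, and Discussion, Overview). Dilution or differential early loss would carry over into that planning.

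**Working it through.** **1. Order of events**

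| Step | Timing | Section |
|---|---|---|
| Eligibility decided by the rTMS team | Before the approach | Recruitment Process |
| Consent signed | Usually about 1 week before rTMS | Recruitment Process |
| Code released | As consent is signed | Randomization and Blinding |
| Arm disclosed | Directly after randomisation | Randomization and Blinding |
| Texts start (one arm) | Day after enrolment | Interventions |
| Motor threshold assessment | About 1 week before rTMS; order relative to consent not stated | Interventions |
| Baseline questionnaire | Asked of those who have consented; Table 1 lists it before randomisation | Data Collection and Follow-Up Assessment; Table 1 |
| First rTMS session | Usually about 1 week after consent | Recruitment Process |

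The open-label gap before rTMS follows directly from these rows. The order of disclosure relative to the baseline PHQ-9, which is the analysis covariate, and relative to the motor threshold assessment is not fixed.

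**2. What intention to treat can recover**

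A participant who withdraws before session 1 has at most a baseline score. Carrying it forward gives a change of baseline minus baseline = 0. If the data are withdrawn as well, nothing remains to carry forward.

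**3. How many patients**

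The stated sample size is internally consistent: 120 + 80 = 200 and 100 + 100 = 200. It is a feasibility number with no dropout rate behind it. Under assumed pre-treatment loss:

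- 200 × 0.05 = 10
- 200 × 0.10 = 20

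**4. Dilution when non-starters stay in (illustration only)**

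Assumptions: 100 per arm, two-sided alpha 0.05, true standardised difference d = 0.4 among starters, and no between-arm difference among non-starters. With non-start fraction f in each arm, the diluted difference is 0.4 × (1 − f), and power ≈ Φ(0.4(1 − f)√(100/2) − 1.96).

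| f | Diluted d | Power | Randomised per arm to keep 100 starters, 100/(1 − f) |
|---|---|---|---|
| 0 | 0.40 | 80.7% | 100 |
| 5% | 0.38 | 76.6% | 106 |
| 10% | 0.36 | 72.1% | 112 |

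If texts alone have some effect, the dilution is smaller, but the estimate still mixes two different questions.

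**5. Loss that differs by arm (illustration only)**

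Let p be the fraction lost in an arm and g the mean outcome of those lost minus the mean of those retained. The retained mean differs from the full-arm mean by −p × g. With an assumed loss of 3% in the text arm and 8% in the rTMS-alone arm, the error in the between-arm difference is 0.08 g(control) − 0.03 g(text). If g is the same in both arms, this is (0.08 − 0.03) × g = 0.05 g, one twentieth of the gap between those lost and those retained. The documents give neither p nor g.

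**The case against.** **Eligibility comes first.** A reader might infer that patients are allocated while their eligibility is still open. The documents do not support that. Recruitment Process says "Participant eligibility will be determined by the rTMS specialist team within the various centers", and the approach and consent follow a favourable decision. It can be argued that this decision concerns the clinical rTMS programme and that trial-specific items, such as a smartphone and good English, are not separately placed in time. That shows only that the article does not spell out the check, not that the check comes late. The learning-disability exclusion, "as identified through medical history or by the investigator during the assessment process", most naturally refers to the assessment before consent. The one exclusion that could arise later is the last, on the sudden appearance of a hindering condition; it is open-ended and sets no screening step after allocation.

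**Motor threshold is not a screening test here.** It is absent from the inclusion and exclusion criteria and is described as a means of selecting stimulation intensity. Nothing says that a patient can fail it. One phrase in Interventions links it to inclusion in the treatment, but that is too loose to carry the stronger reading. Nor is it shown to follow randomisation.

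**Randomisation is already close to the component under test.** Texts start the day after enrolment, rTMS is common to both arms, and intention to treat keeps non-starters where they were allocated. For participants who remain under follow-up this stands: the consequence is dilution of a comparison still protected by randomisation, not bias. It does not answer the case of those who withdraw, because the article's own withdrawal rule stops collection of their outcomes.

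**The loss rates are assumed.** This also stands. No rate in the documents supports a particular figure.

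**Conclusion.** The concern holds as a matter of timing. Allocation and disclosure take place at consent, usually about a week before rTMS, and the withdrawal rule means that early losses cannot be fully recovered by the planned analysis. It does not extend to a claim that patients of unsettled eligibility are being randomised.

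The severity is minor to moderate. At an assumed 5-10% loss, 10 to 20 of the 200 are affected. If they stay in the analysis and show no between-arm difference, power in the illustration falls from 80.7% to between 76.6% and 72.1%. The bias from differential loss cannot be sized from the documents; in the 3% versus 8% illustration with an equal gap in both arms it is one twentieth of that gap. If few patients are lost before session 1, the effect is negligible. The case for change is that the exposure is avoidable and recruitment had not begun when the article was written.

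**What to change.** Amend Randomization and Blinding so that the code is released only after three things are done: the trial's inclusion and exclusion criteria are confirmed, the baseline PHQ-9 is completed, and the motor threshold assessment is finished. Use a visit already planned, as close as practicable to the first rTMS session. State the order of consent, baseline, motor threshold assessment, randomisation and disclosure in one place.

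Define enrolment as the date of randomisation, so that the existing day-after rule for the texts and the follow-up times counted from enrolment both run from that date. Report consented patients lost before that point as not randomised. State that anyone randomised who does not start rTMS, or who later meets the last exclusion criterion, stays in the intention-to-treat set.

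**Cost.** No visit is added, but more patients will be consented without being randomised, and they must be reported in the flow chart. The change is more than an administrative one: the text start and the assessment clock both move later relative to consent, so the survey-link and message scheduling must be reset to the new date.

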### Interventions

Study participants will be randomized to 1 of 2 treatment interventions (rTMS alone or rTMS plus Text4Support). During the introductory visit to the study sites, participants in both arms of the study will be given a detailed orientation about the rTMS application, and all procedures and activities within each visit will be explained to them. As part of their participation in the rTMS program, all patients will be made to complete some standard measures. Participants will be invited to the various rTMS clinics a week before the commencement of the rTMS sessions to enable them to undergo motor threshold (MT) assessment. MT assessment is essential in that it aids in the selection of the required stimulation intensity for each patient for inclusion in the treatment. It is a measure of the minimum intensity of TMS output needed to elicit a motor response in the participating TRD patients in at least 50% of all attempts.

All MT assessments will be conducted by the rTMS team of experts within the rTMS clinics in the various treatment centers, and the team may involve psychiatrists, nurses, and other health care professionals with the requisite training to perform the assessments. Each TMS assessment session will take about 3 to 5 minutes, and the total time will be within 35 to 45 minutes. This visit timeline will be the same for all study participants. Overall, all study participants will be scheduled to receive 30 sessions of rTMS treatment for 6 weeks according to the schedule pre-established by the Alberta Health Services’ Strategic Clinical Network for Addiction and Mental Health and Nova Scotia Health. The rTMS protocol includes low-frequency (1 Hz) inhibitory stimulation targeting the right dorsolateral prefrontal cortex at 120% MT, with 20 trains (60 pulses/train at 60 s) and a total pulse of 1200 for 20 minutes, and high-frequency (10 Hz) excitatory stimulation targeting the left dorsolateral prefrontal cortex at 120% MT, with 75 trains (intertrain interval of 11 s) and a total pulse of 3000 for 19 minutes. The study will use the MagVenture rTMS machine with a figure-of-8 coil. The angle between the coil and the head will be measured at 45 degrees. The cortex area will be targeted by using the 5-cm technique. The prefrontal cortex stimulation site will be determined as 5 cm anterior further ahead of the motor strip in the parasagittal line. Regarding the issue of adherence to the treatment protocol, the rTMS team of experts will contact each patient to remind them of their sessions whenever they default in order to ensure adherence to the treatment. The patients will be continuously monitored, and an attending nurse will remain with each patient during the whole session, checking on any expected side effects. Complete treatment will be considered as attending at least 25 out of 30 sessions.

Additionally, participants in the rTMS plus Text4Support group of the study will be assisted by a study team member to register into the Text4Support program. The process will require all participants in this arm of the study to input their phone numbers into the Text4Support platform, which will be used to deliver daily messages. Starting a day after enrollment, participants will receive daily supportive text messages designed by mental health therapists, clinical psychologists, psychiatrists, and mental health service users. These messages will be based on cognitive behavior therapy principles crafted to positively enhance the mood of users with depressive symptoms and other related mental health problems of concern. The messages will be preprogrammed into a software program that will deliver the messages automatically to the participants’ mobile phones at 10 AM (Mountain Time) and 12 PM (Atlantic Time), and each participant will receive these messages continuously for 6 weeks.

### Hypothesis

We hypothesize that participants enrolled in the rTMS plus Text4Support treatment arm of the study will achieve superior outcomes compared with the outcomes of participants enrolled in the rTMS treatment alone arm of the study in terms of all outcome measures that will be assessed.

### Data Collection and Follow-Up Assessment

All study participants who provide informed written consent and agree to participate in the study will be asked to complete a baseline assessment questionnaire that captures both demographic and clinical information. Study participants will also be asked to complete various follow-up assessments related to primary and secondary outcome measures at 6 weeks, and 3 and 6 months from enrollment. All self-completed surveys will be completed online on tablets or on participants’ cell phones. Clinician-rated scales will be completed either face-to-face at the study sites or over the phone/video conference with the help of a blinded researcher. All follow-up survey links will be delivered to participants’ cell phones at the designated time points. Two reminder text messages will be sent a day apart to encourage participants to complete the follow-up surveys. Participants who do not complete the online surveys despite receipt of 2 reminder text messages will be contacted by a research team member to ascertain if there are any barriers to survey completion and if any assistance is needed. Qualitative data collection will be in the form of a patient experience questionnaire and a key informant interview via telephone, which will be conducted at 3 and 6 months. Data related to participants’ clinic or program attendance rates and use of health services will be compiled from administrative records by a blinded researcher at 6 months.

### Outcome Measures

The primary outcome measure for the study will be changes in the mean score of the Patient Health Questionnaire-9 (PHQ-9) [86] from baseline to the specified time points for the intervention and control groups. With 9 items, the PHQ-9 is half the length of many other depression measures, has comparable sensitivity and specificity, and is made up of the actual 9 criteria upon which the diagnosis of depressive disorders is based according to the Diagnostic and Statistical Manual of Mental Disorders, Fourth Edition. This instrument has the potential to establish major depressive disorder diagnosis, as well as grade the severity of depressive symptoms [86]. The PHQ-9 has good psychometric qualities with high internal consistency, and Cronbach α values of .86 and .89 were obtained in a study that included 2 separate patient populations [87]. The secondary outcome measure will include the 7-item Generalized Anxiety Disorders Scale (GAD-7) [88]. The GAD-7 score is calculated by assigning scores of 0, 1, 2, and 3 to response categories. The GAD-7 total score for the 7 items ranges from 0 to 21, with a score of 0-4 indicating minimal anxiety, 5-9 indicating mild anxiety, 10-14 indicating moderate anxiety, and 15-21 indicating severe anxiety. The GAD-7 has excellent internal consistency (Cronbach α=.92) and test-retest reliability (intraclass correlation=0.83) [88]. The screen version of the Columbia-Suicide Severity Rating Scale (CSSRS) [89] will be included to measure the suicidal ideation of participants. The CSSRS is made up of 6 questions. Users are required to respond “Yes” or “No” to whether they have thought about suicide, have acted or plan to act, or have attempted or plan to attempt suicide. Each of the 6 questions evaluates a different component of the respondent’s suicidal ideation severity and behavior. This measuring tool is scored as low, moderate, or high risk, depending on positive answers (Yes) to the various questions. If a respondent answers positively (Yes) to question 2, the respondent is instructed to respond to questions 3-5. If a respondent answers “No” to question 2, the respondent may skip to question 6. Responding “Yes” to any of the 6 items may imply a need for referral to a mental health care professional, but responding “Yes” to question 4, 5, or 6 indicates a high risk. The CSSRS intensity of ideation subscale has good internal consistency, with Cronbach α values ranging between .73 and .93 [89]. Additionally, the World Health Organization-Five Well-Being Index (WHO-5) [90] will be employed to measure the quality of life of participants. The WHO-5 is a psychometrically robust questionnaire with high internal consistency (Cronbach α=.923) [91]. The WHO-5 is a short questionnaire made up of 5 simple and noninvasive questions, which assess the subjective well-being of respondents. A respondent is asked to rate how well each of the 5 statements applies to them within the last 14 days. Each of the 5 items is scored from 5 (all of the time) to 0 (none of the time). The raw score therefore theoretically ranges from 0 (absence of well-being) to 25 (maximal well-being). To translate the scores to percentages (from 0 [absent] to 100 [maximal]) as required by scales measuring health-related quality of life, the raw score is multiplied 4. The outcome measures and time points for the study are demonstrated in Table 2.

**Table 2 table2:** Client-oriented outcome measures and time points.

Variable type and construct		Tool	Rater	Time points assessed			
				Baseline	1 month	3 months	6 months

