**Methods:**

This study is a multicenter, prospective, parallel-design, 2-arm, rater-blinded randomized controlled pilot trial. The recruitment process is scheduled to last 12 months. It will involve active treatment for 6 weeks, observation, and a follow-up period of 6 months for participants in the study arms. In total, 200 participants diagnosed with TRD at rTMS care clinics in Edmonton, Alberta, and rTMS clinics in Halifax, Nova Scotia will be randomized to 1 of 2 treatment arms (rTMS sessions alone or rTMS sessions plus Text4Support intervention). Participants in each group will be made to complete evaluation measures at baseline, and 1, 3, and 6 months. The primary outcome measure will be the mean change in the scores of the Patient Health Questionnaire-9 (PHQ-9). The secondary outcome measures will involve the scores of the 7-item Generalized Anxiety Disorders Scale (GAD-7), Columbia-Suicide Severity Rating Scale (CSSRS), and World Health Organization-Five Well-Being Index (WHO-5). Patient data will be analyzed with descriptive statistics, repeated measures, and correlational analyses. Qualitative data will be analyzed using the thematic analysis framework.

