### Data Analysis

SPSS Version 26 (IBM Corp) will be used to analyze all quantitative data in accordance with the CONSORT guidelines [92]. Following an intention-to-treat approach, data will be analyzed with descriptive statistics, repeated measures, and correlational analyses. Descriptive data for baseline parameters will be presented using frequencies and percentages among the 2 intervention groups and compared using the chi-square test for categorical variables and the independent sample *t* test for continuous variables. The type of intervention (rTMS alone and rTMS plus Text4Support) will be considered the independent variable, while the scores of the various scales at each time point (6 weeks, and 3 and 6 months) will be considered the dependent variables for each of the analyses. Baseline scores of the respective scales will be used as covariates in the analyses.

To compare the effectiveness of the treatment interventions for the management of TRD among participants, the 1-way between-group analysis of covariance (ANCOVA) comparing changes in the mean scores from baseline to 6 weeks, and 3 and 6 months for all measures will be employed. Preliminary checks will be conducted to ensure there is no violation of the assumption of normality, linearity, homogeneity of variance, homogeneity of regression slopes, or reliable measurement of the variate before ANCOVA is conducted. For participants with missing data, the last observation will be imputed before performing sensitivity analyses of covariance to explore the impact of the imputation of data loss on the PHQ-9 and the secondary measures at each time point.

The chi-square test or Fisher exact test will be employed to compare the prevalence of depression symptoms using the PHQ-9, the prevalence of anxiety symptoms using the GAD-7, suicidal ideations using the CSSRS, and quality of life using the WHO-5 between the 2 intervention groups at all time points in the overall sample.

Furthermore, a paired *t* test will be used to examine the changes in the mean scores of the PHQ-9, GAD-7, CSSRS, and WHO-5 at baseline and 6 weeks for participants who complete the instruments at both time points. Frequencies and percentages will be used to report categorical variables, while mean scores, confidence intervals, and effect sizes will be used to report continuous variables. The 2-tailed α-level criterion for statistical significance will be set at *P*≤.05.

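### No primary time point is named for PHQ-9, so the primary outcome is tested between arms at three visits, each at P≤.05, with no order or adjustment

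*Protocol article*

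**What the plan says.** Outcome Measures sets the primary outcome as "changes in the mean score of the Patient Health Questionnaire-9 (PHQ-9) [86] from baseline to the specified time points" for the two groups. The Abstract also names PHQ-9 mean change as primary and attaches no time point to it.

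Data Analysis makes each visit a separate outcome: "the various scales at each time point (6 weeks, and 3 and 6 months) will be considered the dependent variables for each of the analyses". The between-arm comparison is a "1-way between-group analysis of covariance (ANCOVA) comparing changes in the mean scores from baseline to 6 weeks, and 3 and 6 months", and "Baseline scores of the respective scales will be used as covariates in the analyses". One criterion covers every test: "The 2-tailed α-level criterion for statistical significance will be set at *P*≤.05".

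The Hypothesis section expects superiority of the combined arm on all outcome measures. No section names a primary visit, a testing order, a multiplicity adjustment, or a rule on how many visits must be significant.

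**The concern.** As written, PHQ-9 gets three between-arm tests, and a significant result at any one of them would meet the definition of the primary outcome. The .05 criterion then applies to each test but not to the claim that the primary outcome favours one arm.

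The three visits also ask different questions. Under Interventions, the messages run for 6 weeks, so a comparison near the end of that period measures the effect of receiving them, while 3 and 6 months measure whether it lasts.

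The Introduction and the Discussion both say the trial should supply effect-size data for planning a full-scale trial. With three candidate visits and none designated, a later choice of the most favourable one would tend to overstate that effect.

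**Working it through.** **Inputs from the article**
- Two-tailed significance criterion: .05 (Data Analysis).
- Between-arm ANCOVAs of the primary outcome: 3, at 6 weeks, 3 months and 6 months (Data Analysis).
- Covariate: baseline score of the same scale (Data Analysis).

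**Assumption.** The article gives no correlation between visits, so it is varied from 0 to 0.9.

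**Step 1: the article's own figure.** With one test, the false-positive rate is 1 − 0.95 = 5%. The .05 criterion is therefore the error rate of the primary comparison only if there is a single primary test.

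**Step 2: three independent tests.** Either direction: 1 − 0.95³ = 1 − 0.857375 = 14.3%. In favour of Text4Support only: 1 − 0.975³ = 1 − 0.926859 = 7.3%. The Bonferroni upper bound is 3 × .05 = 15%.

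**Step 3: correlated tests.** With no true difference, the three test statistics are treated as trivariate normal with a common correlation. The rate is P(max|Z| ≥ 1.96) for either direction and P(max Z ≥ 1.96) for the favourable direction, from 4 million simulated draws.

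| Correlation between test statistics | Any visit significant, either direction | Any visit significant, favouring Text4Support |
|---|---|---|
| 0 | 14.3% | 7.3% |
| 0.3 | 13.6% | 6.8% |
| 0.5 | 12.5% | 6.3% |
| 0.7 | 10.9% | 5.5% |
| 0.8 | 9.8% | 4.9% |
| 0.9 | 8.4% | 4.2% |

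The comparators are 5% and 2.5%.

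**Step 4: other correlation patterns.**
- If correlation decays with time (first-order autoregressive, 0.5 to 0.8 between adjacent visits), the two-sided rate runs from 12.9% down to 10.3%.
- Baseline adjustment lowers the correlation that matters. If all visits, including baseline, share a raw correlation ρ, the correlation after adjustment is (ρ − ρ²)/(1 − ρ²). For ρ = 0.3 this is 0.21/0.91 = 0.23, and for ρ = 0.8 it is 0.16/0.36 = 0.44. The two-sided rates are 13.9% and 12.9%.

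**Step 5: after correction.** One named visit gives 5%. Keeping three co-equal visits at .05/3 = .0167 each gives 4.9%, 4.5% and 3.9% at correlations 0, 0.5 and 0.7.

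**The case against.** **It is a pilot.** The trial assesses initial effectiveness, its sample size comes from availability rather than a power calculation, and confirmatory claims belong to the later trial. This stands as a reason for lower severity. It does not remove the point, because the article still states a superiority hypothesis and a significance criterion.

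**The analysis plan may settle it.** Ordering and adjustment are often left to that document, which is not shown. The time point, however, is part of the primary outcome definition, and the article has set it as several visits.

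**Other text may supply a single test.** Repeated measures analysis is mentioned, but the between-arm comparison of means actually specified is a one-way ANCOVA on the scores at each visit. The paired t test at 6 weeks compares each participant with baseline, not one arm with the other. Superiority on all outcome measures is a hypothesis, not a rule that all visits must succeed.

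**Estimates at every visit are useful.** This is fair. The article plans confidence intervals and effect sizes, and seeing all visits can help in choosing the later trial's endpoint. The harm is limited to not having said in advance which estimate is the main one.

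Three stronger readings are tempting and are not supported:
- A reader might infer that the article promises a 5% error rate for the primary claim and breaks it. It states a criterion for tests in general and promises no familywise rate.
- A reader might take the two-sided figure as the chance of falsely declaring Text4Support superior. That chance is about half as large, as the last column of the table shows.
- A reader might count the chi-square or Fisher tests of PHQ-9 prevalence as further chances on the primary outcome. The primary outcome is a change in mean score, so a prevalence difference would not meet it. The article also states no cut-off from which a rate could be computed.

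**Conclusion.** The point holds. The primary outcome has three between-arm tests and no designated time point. The chance of at least one false-positive arm difference on it is about 8-14% two-sided, or about 4-7% against 2.5% in favour of Text4Support. The range rests on assumed visit correlations of 0 to 0.9. Even at 0.9 the two-sided rate is 8.4%, so the conclusion does not depend on the exact value. The visit that will supply the planning effect size is also unspecified.

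In a pilot this should be corrected, but it does not undermine the trial. Nothing in the article indicates an intention to select the most favourable visit; the wording merely leaves that possible.

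**What to change.** Before recruitment, which the Results section says had not begun, amend Outcome Measures and Data Analysis as follows:

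- Name one visit as the primary time point for the baseline-adjusted between-arm difference in PHQ-9, tested once at two-sided .05. The first follow-up, nearest the end of the 6-week intervention, is the natural choice. A later visit would be defensible if durability, which the article lists as a strength, is the main question.
- First reconcile when that visit occurs. The Abstract and Table 2 give 1 month, while Study Design and Setting, Data Collection and Follow-Up Assessment, and Data Analysis give 6 weeks. Follow-up is also timed from enrollment, and Recruitment Process places consent about 1 week before rTMS starts. A 6-week visit may therefore fall before a 6-week rTMS course ends (1 + 6 = 7 weeks). The amended text should state the anchor.
- Make the other two visits secondary, either tested in a fixed sequence after the primary visit or reported as estimates with 95% confidence intervals.
- Label the PHQ-9 prevalence comparisons as supportive.

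The cost is a wording amendment, with no extra participants or data. The small downside is that a difference seen only at another visit could not be claimed as the primary result.
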